#### Covariates

Model-based estimates of intervention effects on the outcomes of readmission, length of stay, use of optimal drug therapy, patient satisfaction, and use of paging devices will employ patient-level and team-level covariates. Patient-related factors to be controlled will be patients' age and gender.

Other covariates will be measures of hospital health care processes hypothesized to be related either to outcome measures or to intervention uptake. The intervention's focal concern is the improvement of interprofessional performance of GIM teaching teams. Therefore, we propose to use the following constructs as structural indicators of functional team processes of care:

• *Ward-based assignment of medical, nursing, and allied health professional staff*. 'Ward basing' refers to hospital practices specifying the deployment of healthcare staff members to a single physical ward location. This arrangement is in contrast to assignments that have staff members working among different medical teams or nursing units as they treat patients. For example, if nurses and nursing units are fixed to physical ward locations, then medical team and professional health staff members could be assigned to patients in such a way that they are required to work with members of several different nursing units. If so, they are said to 'cross teams or units.' On the other hand, if medical teams are fixed to physical ward locations, then it is possible that nurses and professional health staff could be required to work among multiple different medical teams. It is also possible that both medical teams and nursing units are given fixed assignments to single ward locations and professional health staff are assigned to work across multiple combinations of medical teams and nursing units. All of these configurations create variation in the degree to which GIM staff are consolidated to work in one physical location.

Work assignments that see GIM staff consistently – and as a matter of hospital policy – working in multiple physical locations, where work colleagues are more likely than not to be unfamiliar, might have negative impacts on achievement of effective interprofessional collaboration and patient outcomes. An indicator variable will be developed to code whether clinical teaching teams are organized to consolidate interprofessional teams and team members to a single physical ward location.

• *Team-dedicated discharge planner/coordinator*. GIM divisions in some TAHSN hospital sites utilize identified individuals in discharge planning roles as Discharge Planners or Discharge Coordinators. In other sites the discharge coordination function is a responsibility of licensed social workers. We suggest both that patient outcomes with respect to readmission and length of stay, and increased team collaboration and coordination, are influenced positively when the role of discharge planning is performed by an individual with dedicated, team-focused discharge responsibilities (e.g., a registered nurse) instead of an individual with discipline-specific responsibilities (e.g., a social worker). Measured at the level of the clinical teaching team, this construct will be a binary coding of whether the team employs a full-time discharge planner (typically a registered nurse), a social worker with additional responsibilities of coordinating discharge planning, or another individual.

• *Length of regularly scheduled meeting time for interdisciplinary rounds, per team*. We define an 'interdisciplinary round' as a patient-focused meeting that occurs at least one day per week (Monday to Friday), every week, where regular attendance is expected by a team resident physician and leaders of two other clinical professions, nursing and allied health professional staff. The variable will be measured at the level of the clinical teaching team, operationalized as average (mean) meeting hours per week during the time the intervention is implemented at the hospital site.

• *Nursing staff characteristics*. Measures will be developed to adjust for team-level variation in nurse staffing. It is expected that hospital administrative data will be available to enable development of measures of nursing staff characteristics such as: (1) the mean of the daily proportion of registered nurses in a team's staffing mix while the intervention was in progress, or (2) the mean of the daily proportion of nurses with baccalaureate degrees who worked on a team while the intervention was in progress, and (3) the proportion of a team's nursing hours performed by registered nurses per unit of time, or (4) the proportion of a team's nursing hours performed by baccalaureate-prepared nurses per unit of time.

• *Nursing workload measures*. Data are expected to be available to measure team-level variation in nursing workload. Measures will be continuous variables and could include: (1) the patient-to-nurse ratio per unit of time during the intervention period, per team; (2) the mean number of hours of nursing care worked on a team, per patient-day during the intervention period; or (3) nurses' acuity-adjusted patient load per unit of time during the intervention, per team.

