#### Paging activity

For investigations of paging activity, potential subjects are GIM staff members who carry and use a hospital paging device. Development of a paging activity dataset will require assistance from two key resources: (1) GIM administrative functions that can identify GIM team members who carry pagers, and (2) reporting functions in a hospital site's information and communications technology division that can generate analytic reports of pages placed to GIM team members.

Administrative assistants in the hospital sites' Departments of Medicine will provide on-call schedules for medical staff members. On-call medical staff members carry pagers to provide coverage in various positions in the Department of Medicine, including GIM. Patient care managers in GIM teams will identify for us members of their team's nursing and allied health staff who carry paging devices.

After we have obtained the required information to identify individuals and positions in GIM that carry pagers, we will approach information technology reporting functions with the information. When we supply titles of GIM positions that carry pagers and paging identification numbers assigned to them, information technology staff is able to generate reports that can be used to determine the number of pages received by a specific paging identification number, and some other important characteristics of pager calls, chiefly, their designation as urgent or normal.

Recently we undertook exploratory conversations with members of two hospital sites' information technology divisions. Our goal was to probe the general character of paging records (i.e., data fields, content, frequency) that might be available for research use. These conversations suggested two key factors for consideration. First, while the nature of the request and the use of the data or reports in which the data routinely appear would be unusual, it is possible to generate time-delimited reports of activity on a selectively targeted group of paging devices. The second factor we learned is that there is a possibility that calls to paging devices can contain patient health information or other identifying information, and this information could also appear in administrative records of paging activity.

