We appreciate the need to grant supreme confidentiality to both patient information and non-patient-related thoughts and expressions that staff members might convey to one another in their paging activity. For these reasons we will limit our requests to include only the minimum essential amount and character of information required to test our hypotheses. In particular, we will request that staff of the sites' information technology departments *remove/exclude *all personal health information and patient identifying information from any records and reports that are provided to us. This would include text that could appear in records relating to paging devices with alphanumeric capability.

We will request that information technology staff members *include *in records or reports: the number of the device receiving the page, the role/function to which it is assigned (e.g., Patient Care Manager, Occupational Therapist, Attending Staff Physician), the date and time the page was received by the device, the urgent/non-urgent status associated with the page and, if possible, the number and role/function which placed the call to the paging device.

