#### Paging activity

Recent research has suggested that hospital paging systems can be problematic. Paging activity can be highly interruptive. Calls to staff are often clinically inappropriate or not urgent enough to justify a necessary quick callback [33]. Paging can be disruptive to patient care [34] and scheduled rounds [35,36]. Disruptive pages may cause medical errors [37].

If the intervention is implemented correctly, face-to-face communication could increase in frequency and effectiveness. By implication, we suggest that there is potential for reductions in paging activity within and between members of GIM professions.

Administrative records will permit us to examine the total number of pages placed to paging devices of staff members of intervention and control teams, and the number of pages marked as urgent. Numbers of pages to intervention or control teams will be standardized by the number of individuals who carry pagers in the groups. Intervention-control group differences will be examined with linear mixed models.

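### Paging is to be adjusted for patients' age and gender, which the pager records cannot supply, while pager role, which they can, has no stated place in the analysis

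*Protocol article*

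**What the plan says.** Three parts of the protocol article bear on this.

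- **Statistical methods, Covariates.** Five outcomes are named together: readmission, length of stay, optimal drug therapy, "patient satisfaction, and use of paging devices will employ patient-level and team-level covariates". The next sentence reads "Patient-related factors to be controlled will be patients' age and gender". Paging is given no exception. The staff collaboration survey is not on the list. The other covariates are five team constructs: ward basing, discharge planner, time in interdisciplinary rounds, nursing staff characteristics and nursing workload.
- **Outcomes: measurement, Paging activity.** The "potential subjects are GIM staff members who carry and use a hospital paging device". Information technology staff are asked to take out "all personal health information and patient identifying information from any records and reports that are provided to us", including text on alphanumeric devices. The fields requested are the device number, "the role/function to which it is assigned (e.g., Patient Care Manager, Occupational Therapist, Attending Staff Physician"), the date and time, the urgency and, if possible, the number and role of the caller. After talks with two sites, the section reports that "it is possible to generate time-delimited reports of activity on a selectively targeted group of paging devices".
- **Statistical methods, Paging activity.** "Numbers of pages to intervention or control teams will be standardized by the number of individuals who carry pagers in the groups". Arms are then compared with linear mixed models. Neither pager role nor an earlier page count is mentioned.

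**The concern.** The covariate rule names a data source that paging does not have. A page is an event on a staff member's device. Once patient information is stripped, no patient's age or gender can be attached to it, so whoever analyses hypothesis 6 must depart from the stated rule. The Blinding section says paging data will be managed by staff close to the intervention, so a covariate set improvised after the data arrive is open to data-driven choice.

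Standardizing by the number of carriers also treats every pager alike. If some roles are paged more than others, two teams with different role mixes will differ in pages per carrier with no intervention effect. With ten teams per arm, such differences add noise and can fall unevenly by chance.

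**Working it through.** The article gives no power or precision figure for paging. Its power statements concern readmission and do not enter here. The first two steps use the article's own facts. The rest are illustrations with assumed inputs.

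**1. Does the stated adjustment fit the data?** The rule requires patient age and gender. The requested paging fields are device, role, date and time, urgency and possibly the caller. None identifies a patient, and the article has any patient information removed. The patient-level adjustment has no row to attach to.

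**2. Cost of the only substitute, team-mean age and gender.** Inputs: 20 teams in 5 site strata (Sample size; Sequence generation), one treatment term, and one variable for each of the five team constructs. Residual degrees of freedom at team level:

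- after site and treatment: 20 − 5 − 1 = 14 (two-sided 5% t critical value 2.14)
- after the five constructs: 14 − 5 = 9 (2.26)
- after team-mean age and gender: 9 − 2 = 7 (2.36)

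**3. Can role mix alone shift pages per carrier?** Assume one role gets k times the pages of the others and makes up 60% of pagers in one arm and 50% in the other. With no intervention effect, the ratio of pages per carrier is (0.6k + 0.4)/(0.5k + 0.5):

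- k = 2: 1.6/1.5 = 1.07
- k = 3: 2.2/2.0 = 1.10
- k = 5: 3.4/3.0 = 1.13

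**4. How much precision could role recover?** Simulation of 20 teams over 56 days. Assumptions: 4-8 physician and 2-5 other pagers per team, drawn independently for each team, and a between-team SD of 10%. The table gives the standard error (SE) of the log rate ratio.

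| Pages per day, physician v other | SE without role | SE with role | Variance reduction |
|---|---|---|---|
| 8 v 4 | 0.052 | 0.045 | 1 − (0.045/0.052)² = 25% |
| 12 v 3 | 0.063 | 0.045 | 1 − (0.045/0.063)² = 49% |
| 10 v 2 | 0.067 | 0.046 | 1 − (0.046/0.067)² = 53% |

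The SE with role is almost all between-team variation: 0.10 × √(1/10 + 1/10) = 0.045.

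**5. Sensitivity to the assumptions.** The variance due to role mix is 0.052² − 0.045² = 0.00068 at the low end and 0.067² − 0.046² = 0.00237 at the high end. Hold these fixed and raise the between-team SD s, so that the remaining variance is 0.2s²:

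- s = 20%: 0.00068/(0.008 + 0.00068) = 8%, to 0.00237/(0.008 + 0.00237) = 23%
- s = 30%: 0.00068/(0.018 + 0.00068) = 4%, to 0.00237/(0.018 + 0.00237) = 12%

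If all four teams in a site share one role mix, allocation of two teams to each arm within site removes the role effect. The simulated SE is then about 0.045 with or without role, so there is no gain.

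**6. An earlier page count.** If it correlates r with the trial-period count, adjustment leaves 1 − r² of the variance: 0.91 at r = 0.3, 0.75 at 0.5, 0.51 at 0.7. The article gives no value of r.

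**The case against.** The strongest defence is that the covariate statement is one collective sentence over five outcomes. It may mean patient covariates for patient outcomes and team covariates for team outcomes, and the five team constructs are usable for paging. That reading is sensible, but the text does not state it: paging is named and no outcome is exempted.

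Several stronger readings are tempting, and the article does not support them.

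- *The paging analysis cannot be run at all.* Team-mean age and gender could be built from the discharge data linked to teams, and step 2 shows that such a model still has residual degrees of freedom. Only the patient-level adjustment is impossible.
- *One figure per team leaves nothing for a mixed model.* The article does not fix the level of the rows. Device, date and time are requested, and teams nest within hospitals, so a mixed model can be fitted even to team-level values.
- *Role mix is the main reason why teams differ in pages per carrier.* Nothing in the article shows this, and it does not document variation in pager mix within a site.
- *Omitting role and earlier counts is itself an error, or biases the comparison.* Taken alone, the omission is detail that an analysis plan may add; requesting the role field suggests some use is intended. Randomization within site protects against systematic bias.
- *Earlier counts are available.* The article says only that time-delimited reports are possible, after talks with two of five sites. It neither requests nor rules out a pre-intervention window.

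**Conclusion.** The point holds in a limited form. The stated age and gender adjustment does not fit the paging data, and no other section makes an exception. That conclusion rests on the text alone. The carrier-only standardization is a weaker matter: it passes over a variable that the article already requests and that can explain differences in pages per carrier.

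The size of the gain is unknown. On assumed inputs, accounting for role recovers from none of the variance (role mix shared within site) through about 4-23% (between-team SD of 20-30%) to about 25-53% (SD of 10%, mix varying between teams). The benefit is precision and protection against chance imbalance for one secondary outcome. The primary readmission analysis is unaffected. The correction is worth making because it is cheap and hypothesis 6 is prespecified.

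**What to change.** 1. In the Covariates section, exempt use of paging devices from the age and gender rule.
2. In the Paging activity section under Statistical methods, analyse pages by pager position, with role/function as a covariate and with team and site accounted for.
3. Where a site's information technology office can supply it, extend the report to a pre-intervention window and adjust for the earlier page count of the same position or team.

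Items 1 and 2 cost only wording, since role is already a requested field. Item 3 needs a longer date range in a report already being requested. It must be squared with the article's commitment to request only the minimum information needed, and its feasibility is not confirmed beyond the two sites consulted.

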### Outcomes: measurement

#### Readmission data

The Discharge Abstract Database (DAD) is managed by the Canadian Institute for Health Information. The DAD contains demographic, diagnostic, procedural and hospitalization data on hospital discharges (i.e., inpatient, acute, chronic, rehabilitation) and day surgeries in Canada. Data in the DAD can be used to identify dates of index hospital admissions and, subsequently, readmissions. A subset of the DAD relating to Ontario hospital admissions is held at the Institute for Clinical Evaluative Sciences (ICES) in Toronto, Ontario. ICES is an independent, non-profit organization with a core mission to conduct research that contributes to the effectiveness, quality, equity and efficiency of health care and health services in Ontario.

To develop a data file of hospital readmissions among patients discharged from CTTs participating in the SCRIPT Programme, we will use information in the DAD to establish a link between patients and the team that treated them. The key to using this method successfully lies in our identification of a patient's most-responsible physician. In Ontario, all practicing physicians are required to register with the province's regulatory body, the College of Physicians and Surgeons of Ontario (the CPSO). The CPSO assigns every registered physician a unique registration number. This number is a data field in the DAD; it appears on a discharged patient's record line. It is also publicly available with the physician's name on the Internet site of the CPSO.

Leaders of GIM divisions will provide us with the names and team assignments of physicians who were on rotation in GIM CTTs during SCRIPT's intervention periods. When we know a physician's name from GIM records, we can search for his or her profile in the CPSO Internet site. Physicians' CPSO registration numbers will serve as the link between their positions in GIM CTTs and discharge information in the DAD. We will compile a list of registration numbers of physicians who served in GIM during the study period, submit the list to database managers at ICES, and obtain a data set containing de-identified records of patients treated by a physician who served in GIM during the SCRIPT intervention period. In this way we will be able to determine the CTT where a patient received treatment.

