The readmission dataset will be constructed with criteria similar to van Walraven et al. [20]. Patients will be identified as eligible for the readmission pool if they had a nonelective admission to one of the participating sites' GIM divisions through its medical or surgical department, were discharged alive from the participating site's GIM division in the same index admission, and had a nonelective medical or surgical readmission to any Ontario hospital within either 7 days or 30 days of discharge of the index admission. Patients will be excluded if they were admitted from or discharged to another hospital in the index admission; if they had no patient identifier or an invalid identifier; if they lacked key information; or if they exceeded the 99^th ^percentile of distributions of the following variables for all Ontario hospitals: hospital length of stay, number of previous hospitalizations, number of follow-up visits, or case resource consumption.

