#### Readmission

Two patient follow-up periods will be investigated for unplanned hospital readmission: the primary outcome, 30 days post-discharge, and a secondary outcome period of seven days post-discharge. Discharge records will be examined for patients discharged to home between one week after intervention period commencement and one month after intervention conclusion. Readmission proportions will be calculated for patients discharged from intervention and control group teams. The significance of the difference in proportions will be tested with chi-square and association statistics adjusted for the cluster randomized design [29-32]. The primary aim of the trial is to estimate the population-level intervention effect on binary-coded readmission outcomes; consequently, generalized estimating equations will be employed to control for clustering.

Some patients could have multiple hospital admissions, possibly to different hospitals during the study period. Furthermore, some of the admissions may qualify as an "outcome" while others do not. This situation raises a possibility that patients could change clusters (teams) during the trial, by being readmitted to a different GIM team within the same hospital that discharged them earlier in the intervention period. Therefore, a patient will contribute an observation to the analysis only from their first admission during the intervention period. If the readmission is to a different hospital than the index admission, then the readmission is 'credited' to the hospital of the index admission.

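### Patient-level adjustment stops at age and gender, although the eligibility rule already calls for each patient's number of previous hospitalizations

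*Protocol article*

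**What the plan says.** The Covariates section of the protocol article governs "Model-based estimates of intervention effects on the outcomes of readmission, length of stay, use of optimal drug therapy, patient satisfaction, and use of paging devices". For patients, the list is closed: "Patient-related factors to be controlled will be patients' age and gender". The rest are described as follows: "Other covariates will be measures of hospital health care processes hypothesized to be related either to outcome measures or to intervention uptake". The ones named are ward basing, a dedicated discharge planner, time spent in interdisciplinary rounds, nursing staff characteristics and nursing workload. All are team-level measures.

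The Readmission data section excludes patients above the 99th percentile, for all Ontario hospitals, of "hospital length of stay, number of previous hospitalizations, number of follow-up visits, or case resource consumption". On the source it says: "The DAD contains demographic, diagnostic, procedural and hospitalization data on hospital discharges".

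Under Statistical methods, the Readmission section names two follow-up periods, "the primary outcome, 30 days post-discharge, and a secondary outcome period of seven days post-discharge", and states that "generalized estimating equations will be employed to control for clustering". Each patient contributes only the first admission in the intervention period. The stated aim is a population-level effect.

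**The concern.** The exclusion rule cannot be applied unless someone holds each patient's count of previous hospitalizations. The plan uses the count to remove extreme patients and makes no further use of it for those who remain. Because only the first admission in the intervention period is analysed, hospitalizations before it precede the patient's exposure to the intervention. The count is therefore a legitimate baseline adjuster, and a history of admissions is likely to be prognostic for another admission.

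Nothing else in the covariate list does this job. The closest item is an acuity-adjusted nurse load, one of several optional workload measures. It is a team-level figure taken during the intervention, not a measure of patients' prior risk.

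Two things are at stake. One is precision, which matters most in the plan's own second scenario, where power is 67%. The other is chance imbalance. With two teams against two in each of five sites, the arms can differ by chance in their share of frequently admitted patients, and age and gender may not capture that difference.

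**Working it through.** **Inputs from the Sample size and Sequence generation sections.** ICC 0.01; 200 patients per team; 20 teams, 10 per arm; significance level 0.05, taken as two-sided because the one-sided version gives 96.7% and 77.7% and does not match; rates of 10% versus 5% and 5% versus 2.5%.

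**Step 1: reproduce the stated power.**
- Design effect = 1 + (200 − 1) × 0.01 = 2.99.
- Effective n per arm = 10 × 200 / 2.99 = 668.9.
- Power = Φ{[d√n − 1.96√(2p̄(1 − p̄))] / √(p₁(1 − p₁) + p₂(1 − p₂))}, where d is the rate difference and p̄ the mean rate.
- 10% versus 5%: (1.2932 − 0.7301) / 0.3708 = 1.52, so power is 93.6% (stated 93%).
- 5% versus 2.5%: (0.6466 − 0.5266) / 0.2681 = 0.448, so power is 67.3% (stated 67%).

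Both stated figures are reproduced.

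**Step 2: let the covariate explain some variance.** The design effect splits into a within-team part, 1 − 0.01 = 0.99, and a between-team part, 200 × 0.01 = 2.00. The between-team share is 2.00 / 2.99 = 0.67. With a covariate the total becomes

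f = 0.99 × (1 − R²within) + 2.00 × (1 − R²between),

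and the effective n per arm is 2000 / f. The documents give no R², so every row below the first is an assumption.

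| R² within | R² between | f / 2.99 | Power, 10% v 5% | Power, 5% v 2.5% |
|---|---|---|---|---|
| 0 | 0 | 1.00 | 93.6% | 67.3% |
| 0.05 | 0 | 0.98 | 93.9% | 68.0% |
| 0.10 | 0 | 0.97 | 94.3% | 68.7% |
| 0.02 | 0.02 | 0.98 | 94.0% | 68.2% |
| 0.05 | 0.05 | 0.95 | 94.6% | 69.5% |
| 0.10 | 0.10 | 0.90 | 95.6% | 71.8% |
| 0.02 | 0.20 | 0.86 | 96.4% | 73.8% |
| 0.05 | 0.50 | 0.65 | 99.1% | 84.8% |

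Example, the row with both R² at 0.05: f = 0.99 × 0.95 + 2.00 × 0.95 = 2.8405 and n = 704.1, which gives 94.6%.

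**Step 3: size of chance imbalance.** Assumptions, none from the documents: 20–40% of patients have a previous admission; their risk of readmission is 2–3 times that of the others, with 10% overall; the ICC of previous admission is 0.01–0.05.
- SD of the between-arm difference in prevalence π = √[2π(1 − π)(1 + 199 × ICC) / 2000].
- Risk difference between patients with and without a previous admission = r₀(RR − 1), where r₀ = 0.10 / (1 − π + π × RR).
- Low end (π = 0.2, RR = 2, ICC = 0.01): SD 2.19 points × 0.0833 = 0.18 points on the readmission difference.
- High end (π = 0.3, RR = 3, ICC = 0.05): SD 4.80 points × 0.125 = 0.60 points.
- SE of the unadjusted difference at 10% in both arms = √(2 × 0.1 × 0.9 × 2.99 / 2000) = 1.64 points. The imbalance therefore makes up about 1% to 13% of its variance: (0.18/1.64)² to (0.60/1.64)².

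Under these assumptions the implied patient-level R² is about 0.01 to 0.04.

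**The case against.** The strongest reply is that this is a choice of covariate, not an error. Adjusting for age and gender is valid, teams are randomised within site, and no stated figure is wrong. All of that stands, and the point is accordingly about efficiency and chance imbalance. It is not a complaint about detail left to an unseen analysis plan, because the article itself fixes the patient-level list.

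The availability of the count is inferred. The eligibility criteria are described as similar to those of a cited study, the percentiles are province-wide, and the data holder supplies a de-identified dataset. It might apply the exclusion itself and not release the field. This stands, so the field has to be requested.

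The calculated gains start from an unadjusted variance and ignore overlap with age, site and the team covariates. Trimming above the 99th percentile also removes the most extreme counts. Both could make the real gain smaller.

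A reader might infer more than the documents support:
- **That the count is the baseline version of the primary outcome.** The outcome is a binary unplanned readmission within 30 days. The count has no stated look-back period and no split between elective and nonelective stays. It is a prognostic analogue.
- **That power would reach about 98% and 79%.** Those figures need a correlation of 0.5 with the team readmission rate, which no section supports.
- **That patients are steered to teams once allocation is known.** The article does not describe how patients are assigned to teams.
- **That a team's readmission rate before the intervention could be added just as cheaply.** Physician rosters are to be obtained only for the intervention periods, medical staff turn over quickly, and a further team-level term is costly with 20 clusters.

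**Conclusion.** The point holds as a modest, inexpensive improvement. The plan leaves out of its outcome models a pre-exposure variable that is probably prognostic and that its own eligibility rule requires.

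Under equal R² of 0.02 to 0.10 within and between teams, the gain is about 0.4 to 2 points of power for 10% versus 5%, and about 1 to 5 points for 5% versus 2.5%. If the count explains only within-team variation, the gain is under 1 point in both scenarios at R² 0.05; at R² 0.10 it is 0.7 and 1.5 points. Larger gains need the count to explain a substantial share of between-team variance, which the documents neither support nor exclude. In the weaker cases the main benefit is protection against chance imbalance.

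The analysis as written is not biased by this omission, and the published power figures stand.

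**What to change.** In the Covariates section, list the patient-level terms as age, gender and number of previous hospitalizations before the index admission, and state the look-back period. Make the change before outcome data are seen.

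Ask the Institute for Clinical Evaluative Sciences to keep that field in the analysis dataset, not only to use it for the exclusion. Enter it in the generalized estimating equations for 30-day and 7-day readmission and in the linear mixed model for length of stay. Report a standardised marginal risk difference from the readmission model, so that the adjusted result still targets the population-level effect the plan names.

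The cost is one patient-level model term, one field in the data request and the standardisation step. No team-level degree of freedom is used.
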